## Abstract

**Background:**

School-based breakfast provision is increasingly being seen as a means of improving educational performance and dietary behaviour amongst children. Furthermore, recognition is growing that breakfast provision offers potential as a means of addressing social inequalities in these outcomes. At present however, the evidence base on the effectiveness of breakfast provision in bringing about these improvements is limited.

**Methods/Design:**

This paper describes the research design of a large scale evaluation of the effectiveness of the Welsh Assembly Government's Primary School Free Breakfast Initiative. A cluster randomised trial, with school as the unit of randomisation was used for the outcome evaluation, with a nested qualitative process evaluation. Quantitative outcome measures included dietary habits, attitudes, cognitive function, classroom behaviour, and school attendance. The study recruited 111 primary schools in Wales, of which 56 were randomly assigned to control condition and 55 to intervention. Participants were Year 5 and 6 students (aged 9–11 years) in these schools. Data were collected for all 111 schools at each of three time points: baseline, 4 month and 12 month follow-up. This was achieved through a repeated cross-sectional survey of approximately 4350 students on each of these occasions. Of those students in Year 5 at baseline, 1975 provided data at one or both of the follow-ups, forming a nested cohort. The evaluation also included a nested process evaluation, using questionnaires, semi-structured interviews and case studies with students, school staff, and local authority scheme coordinators as key informants.

**Discussion:**

An overview of the methods used for the evaluation is presented, providing an example of the feasibility of conducting robust evaluations of policy initiatives using a randomised trial design with nested process evaluation. Details are provided of response rates and the flow of participants. Reflection is offered on methodological issues encountered at various stages through the course of the study, focusing upon issues associated with conducting a randomised trial of a government policy initiative, and with conducting research in school settings.

**Trial registration:**

Current Controlled Trials ISRCTN18336527

## Background

Many school children do not eat breakfast everyday: in a survey of year 6 children (aged 10–11) conducted in the United Kingdom, 5% of children reported having not had anything for breakfast that day, 3% had only consumed a drink and approximately a further 10% reported eating crisps or chocolate for breakfast [1]. Not eating (or 'skipping') breakfast has been associated with a wealth of deleterious health outcomes [2-4] poorer overall nutritional adequacy [5,6] and detrimental effects upon memory and concentration [5-9].

A recent study amongst schoolchildren in Wales focusing upon associations between physical activity, dietary behaviours and obesity indicated that breakfast was the most commonly missed meal amongst all children, with obese children skipping breakfast on average twice a week, double the frequency of normal weight children [10]. Furthermore, studies conducted in the United Kingdom demonstrate a significant social gradient in breakfast eating habits, with children from more deprived backgrounds more likely to skip breakfast than their wealthier counterparts [11-13]. In addition, consumption of poorer quality breakfasts has been found to be associated with higher levels of deprivation, as have unhealthy attitudes towards breakfast [12]. Therefore, promotion of habitual and healthful breakfast eating behaviours may promote population health and academic performance and reduce health and educational inequalities.

In recent years, many efforts to facilitate change in dietary behaviours have been directed towards schoolchildren due to the capacity of such approaches to reach large numbers of children simultaneously [14,15]. Habitual behaviours developed in childhood may track into adulthood, with potential consequences for health later in life [16], and repeated exposure to healthier foods at an early age has been shown to increase the intrinsic rewards associated with their consumption [17-20].

Appropriate manipulation of the school environment may offer an efficient and effective long-term means of improving the health of the population. Furthermore, if such intervention brings about sufficient dietary improvement to impact upon cognitive functioning and behaviour [21], this may translate into improved school performance and educational achievement.

Recognition of these potential benefits has led to a number of government funded school breakfast initiatives (e.g., see Shemilt et al [22]). These were first employed in North America in 1966 and aimed to improve the nutritional status of children in deprived areas [23]. Since then, the number of schools participating in such programmes has risen dramatically, so that by 1997 approximately six million children in the US were attending a school breakfast club each day [24]. In the UK, the introduction of breakfast programmes has occurred more recently, with funding from sources such as the Education Action Zone initiative, New Opportunities Funding and Sure Start out of School Funding. The Department of Health also introduced a pilot initiative in 1999. However, the objectives of these different breakfast clubs have varied considerably; whilst some have focused on the provision of a healthy breakfast, others have placed more emphasis on childcare, education, or informal interaction between children and school staff [22]. Indeed, a "breakfast club" may not necessarily provide breakfast.

Nevertheless, there is evidence to suggest that school breakfast programmes can help improve nutrition and may also be associated with improvements in attendance, academic performance and behaviour (e.g., [7,25-28]). However, findings have been inconsistent [23] and the research has had limitations, with most of the studies unable to incorporate appropriate control groups or suffering substantial contamination between trial arms. Thus although there is good reason to believe that breakfast programmes can have a wide range of beneficial outcomes, this has yet to be convincingly demonstrated.

### The Primary School Free Breakfast Initiative

The Welsh Assembly Government's Primary School Free Breakfast Initiative arose from a Labour Party manifesto commitment to make free healthy breakfasts available to all maintained primary schools in Wales. This paper reports upon the design of a comprehensive national evaluation of this initiative, using a cluster randomised controlled trial design with a nested process evaluation, and discusses issues in the implementation of the evaluation design.

## Methods/Design

### Study design

The evaluation study comprised of two key components. In order to evaluate the overall effectiveness of the intervention, a randomised controlled design was employed. Randomised controlled trials (RCTs) are generally considered the most reliable means of assessing intervention efficacy (e.g., see Campbell et al [29]). Since public health interventions, such as the school breakfast initiative, tend to act at multiple levels and through multiple channels [30] implementation of a traditional RCT is difficult. It is likely that these methodological difficulties have contributed to the absence of good evidence for the efficacy of school breakfast programmes and other public health interventions. However, recent developments in research methodology, including the use of cluster RCTs and mixed methodologies have the potential to provide unbiased estimates of the effectiveness of such interventions as well as identifying other factors that are more variable such as intervention delivery, context and support [31].

As the intervention was implemented at the school-level, randomisation of individual students to control or intervention groups was not practicable. As such the evaluation adopted a cluster randomised design with school as the unit of randomisation. A summary of this study design is presented in Figure 1. In line with the aforementioned development of mixed-methodology approaches to evaluation, a nested qualitative process evaluation was included to address issues concerning the context and implementation of the initiative. In this way, the evaluation not only addressed the question, 'Does it work?', but also considered 'What works?', 'For whom?' and 'Under what circumstances?' [32].

**Figure 1 F1:**
[figure not shown]
Timetable for evaluation of the Welsh Assembly Government's Free School Breakfast Initiative.

### The Primary School Free Breakfast Intervention

The intervention provided a school-based breakfast before the commencement of classes, without any cost being borne by parents. The aim of the intervention was not only to encourage breakfast consumption per se, but to improve the nutritional quality of children's breakfasts. Hence a particular focus was placed upon limiting available food choices to breakfast items considered to be healthful. Provision was therefore offered from four food types: non-sugar coated cereals, bread, milk products and fruits, in addition to drinks. Schools were provided with guidelines regarding how the scheme should be run, in terms of staff to student ratios and the food to be provided, but were given a reasonable degree of autonomy in the operation of the scheme.

The scheme was rolled out in two distinct phases by the Welsh Assembly Government, with initial priority given to schools in more deprived areas of Wales. As such, schools classified as 'Communities First' schools were eligible to receive the intervention initially before the scheme was made available to all schools the following year. At the time of writing, information about the scheme can be found on the Welsh Assembly Government's website [33].

### Recruitment and randomisation of schools

#### Phase one – Communities First schools

In autumn 2004, head teachers of infant, junior and primary schools located in 'Communities First' (i.e. deprived) areas in nine local education authorities (LEAs) in north, south and west Wales were invited to participate in the evaluation. Schools were offered £250 to compensate for additional teacher time and disruption to school activities. One hundred and fifty-two schools were approached and 58 schools agreed to participate. Reasons for non-participation were generally related to the running of the breakfast scheme itself (worries about implementing the new initiative and bringing forward the start date) rather than any concerns over data collection burden. Those that agreed to participate were randomised to the intervention or control condition using strata defined by LEA, school size, free school meal entitlement and Welsh language medium.

#### Phase two – non-Communities First schools

Head teachers of infant, junior and primary schools located in 'Non-Communities First' (i.e. more affluent) areas, in the same nine LEAs were invited to participate in the evaluation. As before, schools were offered £250 to compensate for additional teacher time and disruption to school activities. This time, 456 schools were approached and 53 schools agreed to participate. Again, reasons for non-participation were generally related to fears about relinquishing control over the start date of the scheme, although a number of differences in reasons for non-participation unique to this phase of the study were identified (see response biases section of Discussion). Those who agreed to participate were randomised to intervention or control following the same methods of stratification as described above.

For both phases, schools in the intervention group were asked to set up a breakfast scheme, following the guidance issued by the Welsh Assembly Government, after baseline measures had been collected. Schools in the control condition were asked to refrain from setting up a breakfast scheme until after the 12 month measures had been collected.

In each of these 111 schools, following the timetables set out in Figure 1, one class of Year 5 children (9–10 years) and one class of Year 6 children (10–11 years) were randomly selected to complete class based measures. From this sample, 5 children from each year (i.e. 10 in total) were randomly selected to be assessed by teachers (see below) and 6–9 of these children were randomly selected to participate in individual testing. In addition, for each school 35 children were randomly selected from the full age range, and a questionnaire was sent to their parents. For primary schools, 5 children were sampled from each year group (i.e., reception to year 6) and for junior schools, 8 or 9 students were selected from each year group (i.e., years 3 to 6).

### Outcome measures

The quantitative measures employed in the evaluation aim to provide an accurate assessment of the impact of the scheme on children's dietary habits, cognitive performance, attitudes and classroom behaviour. As previously discussed, since the intervention is implemented at the school-level, randomisation has to take place at this level. As a consequence, relatively large numbers of participants are needed in order to detect any intervention effect. For such a trial to be feasible it is therefore important that the outcome measures employed are relatively quick, cost-effective and easy to implement. In an attempt to address the inevitable tension between measurement precision and sample size/response bias (i.e., brief measures, whilst cost effective and perhaps encouraging higher response rates, are likely to suffer from a higher degree of measurement error) our evaluation incorporated two levels of assessment. For dietary measurement, the study first used a less sensitive dietary recall questionnaire administered simultaneously to the whole class. Secondly, a subsample of children also participated in a validated, and much more time consuming, one-to-one dietary interview procedure.

The following standardised, previously validated measures were used:

#### Cognitive tests

Classroom administered cognitive tests were used to assess episodic memory, working memory, sustained attention and psychomotor speed [34-36]. Individually administered, computerised cognitive tests were used to assess sustained attention, selective attention, simple reaction time and choice reaction time. The most consistent effects of breakfast upon cognition, in experimental conditions, have previously been observed for episodic memory [35,37,38] which was therefore selected as the primary outcome in terms of cognitive function.

#### Strengths and Difficulties Questionnaire

The Strengths and Difficulties Questionnaire [39] was completed by teachers to assess children's classroom behaviour. This was a relatively brief, but well-established measure that assessed five dimensions of behaviour: hyperactivity, emotional symptoms, conduct problems, peer problems and pro-social behaviour. Hyperactivity in particular, is likely to be influenced by breakfast due to its relation to on-task behaviour [40]. Therefore this sub-scale will be analysed as a secondary outcome, with the global total difficulties scale analysed as a tertiary outcome.

#### Dietary recall interview

Individually administered dietary recall interviews were used to provide a more accurate estimate of the impact of the initiative on children's diets. These interviews were conducted using a standardised protocol based on that employed by Lytle et al. [41].

Due to a shortage of previously validated measures the following measures were developed and validated for use in the present study [42,43]:

#### Dietary recall questionnaire

Children were asked to list all foods and drinks consumed at chronologically ordered time points throughout the day (e.g., at home before school, on the way to school, at school before class started). Details of breakfast on the day of reporting (i.e., any foods consumed before the start of classes) were collected first, followed by details of the previous day's intake [42]. Primary measures from this questionnaire are the number of healthy food items (i.e., fruit, bread, cereal and milk products) and number of unhealthy food items consumed at breakfast (i.e., sweet items and crisps), and the number of days on which breakfast was consumed in the last two days (i.e., 0, 1 or 2).

#### Attitudes towards eating breakfast

Attitudes were assessed using a questionnaire containing thirteen statements referring to a variety of domains, such as concentration and behaviour, energy, and the general importance placed on breakfast. Children were asked to indicate the extent to which they agreed or disagreed with each statement by placing a tick in one of 5 boxes (agree a lot/agree a bit/don't agree or disagree/disagree a bit/disagree a lot) [43].

#### Parental questionnaire

The parental questionnaire contained 10 questions designed to assess children's breakfast eating habits. Five of these asked parents how many times on school days their child usually engaged in a particular behaviour (ate breakfast at home, took something from home for breakfast to eat on the way to school or at school before the start of class, took money to buy breakfast on the way to school, ate a breakfast provided by the school, missed breakfast). These were answered by placing a tick in one of 7 boxes (number of days ranging from 0 to 5 or 'Don't know'). Four questions asked parents how many times at the weekend their child usually engaged in a particular behaviour (ate breakfast at home, took something from home for breakfast to eat elsewhere, took money to buy something for breakfast, missed breakfast). These were answered by placing a tick in one of 4 boxes (number of days ranging from 0 to 2 or 'Don't know'). An additional question asked parents to rate the frequency with which they thought their child ate a healthy breakfast. This was answered by placing a tick in one of 5 boxes ranging from 'My child always eats a healthy breakfast' to 'My child rarely eats a healthy breakfast'.

### Sample size calculations

Since there are a range of outcome measures, sample size requirements were calculated using effect sizes. Sample size calculations assume an intra-cluster correlation of 0.02, 80% power, and a two-tailed alpha of 0.05. With 111 schools in the trial, for pupil outcomes from the self-complete questionnaire, assuming an average of 50 responses per school, there will be power to detect an effect size of 0.11. For parent reports of breakfasting behaviour, assuming 20 responses per school, there will be power to detect an effect size of 0.15. For pupil outcomes from the dietary recall interviews, there will be power to detect an effect size of 0.2.

### Data collection

Parents were informed of the research in advance by means of a letter and information sheet either posted to them or sent home with children, and were asked to complete a return slip and/or contact the school if they did not wish their child to participate in the study. At each data collection, children were also informed that they were under no obligation to participate. The study received ethical approval from the Cardiff University Social Science Ethics Committee.

Cognitive tests, the attitudes questionnaire and the dietary recall questionnaire were completed between 9 am and 12 pm as supervised classroom exercises with a maximum class size of 40 children. For the attitudes questionnaire, to minimise conferring and ensure that children worked at the same pace and did not distract one another, the researcher read out the statements one by one and children marked their response for each statement after it was read out. For the dietary recall measure, the researcher read out the instructions and asked children to complete the questionnaire independently from one another. Children were asked to put their hands up when they had finished or if they needed help with spelling, or further clarification of questions. Three members of the research team were present to assist children.

As described above, at baseline and 12-month follow-up only, 3–5 children from each year group (e.g. year 5 and 6) were selected to complete individual tests between 12:30 and 3:30 pm (although timetabling restrictions occasionally led to these being conducted as early as 11:00 am). These were conducted on a one-to-one basis with one researcher guiding each child through the computerised cognitive tests and the dietary recall interview.

Schools were divided between key members of the research team, and each key researcher was responsible for all liaison with their assigned schools, and held principal responsibility for data collections. Two trained temporary research assistants were also brought to each school at baseline and 12-month follow-up, to provide general assistance with group testing and to conduct individual testing in the afternoon. For the first follow up, only one assistant was required as only the morning's group testing was carried out. All temporary research assistants were fully trained and monitored by the key researchers in order to maximise standardisation across the trial sites and data collection sweeps.

### Statistical analyses

There was no one primary outcome, but a pre-specified analysis plan was agreed in which the following were identified as primary outcomes: the proportion of students consuming two breakfasts over two days; episodic memory; number of healthy food items consumed at breakfast and number of unhealthy food items consumed at breakfast according to the dietary recall questionnaire. Secondary outcomes were identified as attitudes towards eating breakfast; rest of day healthy food items; rest of day unhealthy food items; scores on the hyperactivity/inattention scale of the strength and difficulties questionnaire, and parental reports of frequency of eating breakfast at home and at school. A number of other outcome measures were *a priori *defined as tertiary outcomes, including cognitive measures other than episodic memory, the total difficulties score on the strengths and difficulties questionnaire, parental reports of morning routines and child care arrangements before school and variables collected from the individually administered in-depth dietary recall and cognitive measure interviews.

For each outcome variable, the primary analysis is a school-level weighted regression analysis [44] adjusting for baseline score and the four stratification variables. These primary analyses will be conducted on an intention-to-treat basis, in which each school is coded according to the treatment condition to which it has been randomised. A secondary analysis conducted for all variables will be a per protocol analysis, in which schools are coded according to whether or not a free breakfast scheme was set up prior to outcome measurement.

Sub-group analyses are planned for study phase, socio-economic status and groups defined by consumption of breakfast, healthy and unhealthy food items at baseline. Socio-economic status will initially be defined in terms of a school level variable indicating the proportion of students entitled to free school meals, but through further data linkage it is planned that student level socio-economic measures based on postcode of residence will be available. If this additional data linkage is undertaken, it will also allow the performance of students in Statutory Assessment Tests and public examinations to be included as additional (secondary) outcome variables, although this is not included in the current protocol as it is dependent on ethical approval and funding. Other sub-group analyses may be conducted according to variables identified in the process evaluation, which may include measures on the implementation of the scheme or relating to the school and community context.

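### Schools were randomised within two phases, but the primary model does not adjust for phase; including it is nearly free, and any gain in precision is small and conditional

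*Protocol article*

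**What the plan says.** Under Recruitment and randomisation of schools, the protocol article gives each phase its own recruitment and its own randomisation.

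- **Phase one (Communities First areas).** "One hundred and fifty-two schools were approached and 58 schools agreed to participate". They were "randomised to the intervention or control condition using strata defined by LEA, school size, free school meal entitlement and Welsh language medium".
- **Phase two.** The schools were "located in 'Non-Communities First' (i.e. more affluent) areas, in the same nine LEAs". Of these, "456 schools were approached and 53 schools agreed to participate", and they were "randomised to intervention or control following the same methods of stratification as described above".

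The section on the intervention puts the wider roll-out a year after the first. The Response biases section adds that in phase two the scheme was already reaching non-participating schools as the evaluation began.

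Under Statistical analyses, the primary analysis of every outcome is "a school-level weighted regression analysis [44] adjusting for baseline score and the four stratification variables". The same section lists study phase only among the planned sub-group analyses.

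**The concern.** Each phase's schools were allocated as a separate set, so treatment was assigned within phase, and phase works as a fifth stratification factor. The model adjusts for four. LEA cannot stand in for phase, because both phases drew on the same nine LEAs.

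Phase could be prognostic. The two sets differ in area deprivation by construction, and the Background reports a social gradient in breakfast eating. They also differ in the timing and setting of roll-out.

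When a stratum is balanced between arms and related to outcome, leaving it out keeps its variance in the residual although the design has removed that variance from the treatment comparison. The reported standard error is then larger than the true one. What is at stake is a small amount of precision and agreement between analysis and design.

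**Working it through.** **1. The plan's own figure.** Inputs from Sample size calculations and the Abstract: 55 and 56 schools, 50 pupils per school, ICC 0.02, 80% power, two-sided 0.05.

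- Variance of a school mean (SD units): 0.02 + 0.98/50 = 0.0396.
- Standard error of the arm difference: √[0.0396 × (1/55 + 1/56)] = 0.0378.
- Detectable effect: (1.960 + 0.842) × 0.0378 = 0.106 (0.107 with t quantiles). The stated 0.11 is reproduced. It does not depend on phase.

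**2. Degrees of freedom.** Assume 8 df for nine LEAs and 1 df for each other covariate. Residual df = 111 − (intercept 1 + arm 1 + baseline 1 + LEA 8 + other stratifiers 3) = 97. Adding phase leaves 96. The residual mean square changes by the factor (1 − R²) × 97/96, which is below 1 only if R² exceeds 1/97, about 1%.

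**3. Effect of including phase.** R² is the share of residual school-level variance that phase explains beyond the listed adjusters. The article gives no value, so a range is assumed. The standard error is multiplied by √(1 − R²). With phase omitted and arms balanced within phase, the actual type I error is about 2 × [1 − Φ(1.96/√(1 − R²))]. The implied phase gap is √[R² × 0.0396 / (p(1 − p))], with p = 58/111 and p(1 − p) = 0.2495.

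| Assumed R² | Implied gap (SD) | Fall in SE | Detectable effect | Type I error if omitted |
|---|---|---|---|---|
| 1% | 0.04 | 0.5% | 0.1053 | 0.049 |
| 2% | 0.06 | 1.0% | 0.1048 | 0.048 |
| 5% | 0.09 | 2.5% | 0.1032 | 0.044 |
| 10% | 0.13 | 5.1% | 0.1004 | 0.039 |
| 20% | 0.18 | 10.6% | 0.0947 | 0.028 |

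The gaps and detectable effects use the unadjusted variance 0.0396. If the other covariates have already reduced it, the same R² corresponds to a smaller gap.

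**4. Cross-check through the between-school component.** About 4350 pupils in 111 schools is 39.2 per school. The unadjusted between-school share of a school mean's variance is 0.02/(0.02 + 0.98/39.2) = 0.444. Baseline score and free school meal entitlement should shrink the between-school part. If they halve it (assumption), the share is 0.01/(0.01 + 0.025) = 0.286. If phase explains 10-30% of what is left (assumption), the standard error is multiplied by √(1 − 0.286 × 0.1) = 0.986 to √(1 − 0.286 × 0.3) = 0.956, a fall of 1.4-4.4%. This agrees with the 2-10% rows above.

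**5. Power at an effect of 0.11.** For a residual phase gap of 0.10 SD, R² = 0.10² × 0.2495/0.0396 = 6.3%. Power is 83.7% with phase omitted and 85.3% with it included. Both exceed the planned 80%.

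**The case against.** The strongest case against is that the model already carries the reason for expecting phase to matter. Free school meal entitlement is an adjuster, and the Response biases section treats it as the deprivation indicator. Each school's baseline score is also in the model and should absorb much of any stable difference in level, including one due to calendar year. What remains is mainly a phase difference in change from baseline, for which the article offers no evidence. Any error is conservative, and phase is not absent from the plan, since a sub-group analysis is intended.

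Most of this stands, and it is why the size is conditional and small. It does not show that nothing remains. Communities First is an area designation and free school meal entitlement a school measure, so one does not determine the other. On the planning ICC, a baseline school mean has a reliability of only about 0.44, so it removes stable differences incompletely. The roll-out setting could also shift follow-up levels differently in the two phases.

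The agreed analysis plan, which is not shown, may code the strata within phase. The article's stated list of adjusters does not say so.

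Three stronger readings are tempting but not supported:

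- **That precision is certainly lost.** No figure in the article shows that phase predicts outcome once the listed covariates are in.
- **That the standard error would fall by 2-7%, worth 5-15% more schools.** This applies a post-adjustment R² of 10-30% to the unadjusted share of 0.444. With the share at 0.286, the equivalent is about 3-9% more schools (1/0.971 to 1/0.914).
- **That the different recruitment rates (58 of 152 and 53 of 456) show phase to be prognostic.** They bear on representativeness, not on outcome given the covariates.

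**Conclusion.** The point holds as a minor mismatch between design and analysis. Schools were randomised within phase, and the stated primary model does not include phase. Under intention to treat, with arms balanced within phase, the estimate is unbiased; the standard error is too large to the extent that phase remains prognostic. On the assumed R² of 2-10%, the excess is roughly 1-5%, and it vanishes at about 1% or below. The article gives only the overall 56:55 allocation, so balance within phase is itself an assumption.

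A reader might infer that the primary result would be biased or invalid. The documents do not support that.

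The per protocol analysis is less protected. It recodes 15 schools (five control, ten intervention) by whether a scheme was set up, and pressure to start is described differently for the two phases. Phase could therefore confound that comparison. The recoded schools are not broken down by phase, so no size or direction can be given.

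**What to change.** Add a phase indicator to the school-level weighted regression for every outcome, in both the intention-to-treat and per protocol analyses. Alternatively, enter the strata as formed within phase and say so. Keep phase as a planned sub-group, tested by the phase-by-arm interaction; that model needs the phase main effect in any case. Reporting the allocation by phase would let readers check the balance assumption.

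The indicator costs one of about 97 residual degrees of freedom. The critical t value moves only from 1.9847 to 1.9850. No new data are needed, since phase is known for every school.
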